## Procedures

Potential patients will be recruited through advertisements in clinical waiting rooms and via mobile patient recruitment applications, like Wechat (Tencent Ltd, Shenzhen, China). Eligible patients will be 17 to 40 years of age with a history of neck pain for longer than 3 months and who are interested in taking part in a clinical trial of physical therapy. No details of radiographic features of the neck region will be mentioned in the advertisements. Volunteers will contact the project coordinator or physician of the rehabilitation clinic and will undergo an initial screening. A clinical and radiological examination will be used to exclude the presence of a specific cause of neck pain.

Patients will complete a written, informed consent form, provide demographic data and complete a survey of patient-reported outcome measures. An outcome assessor will measure the rotational movements and translational displacements of the head in relation to the thoracic region using GPS.

Following the baseline assessment, a research assistant will randomize patients to a study group and control group using sealed, numbered envelopes and a randomisation list generated by the “random integer generator” (https://www.random.org/integers/). The randomisations will be restricted to permuted blocks of different sizes. Each random permuted block will be transferred to a sequence of consecutively numbered, sealed, opaque envelopes for storage in a locked locker until required. As each patient formally enters the trial, the researcher will open the next envelope in the sequence in front of the patient. A blinded investigator will perform all outcome assessments at baseline, after 10 weeks of intervention and after 3 months of follow-up.

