### Data collection

The primary outcome in the present study will be measured as the feasibility outcomes of conducting an RCT. The secondary outcome will be measured by the visual analogue scale (VAS), neck disability index (NDI) and the 3D posture parameters measured by the GPS device. The primary and secondary outcomes will be measured at baseline, after 10 weeks and after 3 months of follow-up. The schedule of treatment and outcome assessments is presented in Table 1.

**Table 1 Tab1:** Schedule of treatments and outcome measures throughout the trial

	Baseline 0 weeks	Treatment period 10 weeks	Follow-up after 3 months
Measures			
Feasibility outcomes	√	√	
VAS	√	√	√
NDI	√	√	√
3D posture parameters	√	√	√
Treatments			
Ambulatory mirror image functional re-training through wearing 3D adjustable CTPCO		√	
Conventional treatment like moist hot pack, soft tissue mobilization, manual therapy, therapeutic exercise		√	

*VAS* visual analogue scale, *NDI* Neck Disability Index, *3D* three-dimensional, *CTPCO* cervico thoracic posture corrective orthotic

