### Sample-size calculation

The sample size of a future, fully powered study will be estimated using sample-size calculations using the effect-size data from this pilot study. We will recruit 24 patients for two groups [37].

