### Statistical analysis

Results of primary outcome measures will be provided descriptively in tables and compared to the a priori established goals. To provide a recommendation for estimated sample size for a future full-scale RCT, between-group effect sizes and 95% confidence intervals (CIs) with Hedges correction will be calculated for changes in the secondary outcomes of VAS, NDI and 3D posture parameters. The mean ± standard deviation score for each of the subscales will be used in the calculation of the effect size. Estimated sample size will be determined using the between-subject effect size, with a minimum of 80% power (*α* = 0.05). The sample size will be increased to allow for an estimated 20% dropout rate. Statistical methods for the secondary outcome measures will be evaluated via comparisons of changes between groups. Complete case analyses will be performed to include outcomes from all patients who completed baseline and follow-up evaluations, as recommended in the Consolidated Standards of Reporting Trials (CONSORT) guidelines [39]. The between-group difference in change scores for each outcome measure from baseline to follow-up will be determined and reported as the means and 95% CI, using an analysis of covariance. Covariates of age and sex will be included in the analysis. All statistical analyses will be performed in SPSS version 23.0 software (IBM Corporation, Armonk, NY) with significance set at *P* < 0.05.

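### The ANCOVA of change scores names age and sex as covariates but omits the outcome's own baseline value, at a modest cost in precision and protection against chance imbalance

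*Protocol article*

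**What the plan says.** The Statistical analysis section of the protocol article defines the treatment comparison for the secondary outcomes: "The between-group difference in change scores for each outcome measure from baseline to follow-up will be determined" and reported as means with 95% CIs. It then gives the model and the covariates: "using an analysis of covariance. Covariates of age and sex will be included in the analysis". Neither that section nor any other names the outcome's own baseline value as a covariate.

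The baseline values will be available. Data collection states: "The primary and secondary outcomes will be measured at baseline, after 10 weeks and after 3 months of follow-up".

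Procedures describes the allocation: "The randomisations will be restricted to permuted blocks of different sizes". No stratification by baseline severity is described.

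Earlier in Statistical analysis a different calculation is set out for planning the full trial. Hedges-corrected between-group effect sizes "will be calculated for changes in the secondary outcomes of VAS, NDI and 3D posture parameters", using means and SDs. The Primary outcome measure section uses between-group effect size to choose the full trial's primary outcome, and the Sample-size calculation section uses the pilot's effect-size data to set its size.

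**The concern.** Analysing change without baseline in the model fixes the slope of follow-up on baseline at 1. When the true slope is lower, the group that happens to start worse tends to show the larger improvement, whatever the treatment does. In a large trial this averages out. With 24 patients and no stratification on severity, a noticeable baseline difference in at least some outcomes is quite likely, and nothing in the stated model corrects for it. The named covariates deal with it only so far as age and sex happen to track baseline severity.

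At stake is the reported secondary treatment difference and its CI. Estimating the effect of the orthotic is the trial's stated secondary aim. The primary feasibility outcomes are not affected.

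**Working it through.** The plan states no figure to reproduce: 24 rests on a citation, and the 80% power, α = 0.05 and 20% dropout all refer to the future trial.

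**Inputs from the article.** N = 24; change-score ANCOVA with two covariates (age, sex).

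**Assumptions.** 1:1 allocation, so n = 12 per arm; equal SD σ at both visits; age and sex unrelated to outcome; ρ not given, so 0.3 to 0.9 is shown.

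**Chance imbalance.** The SE of the baseline difference is σ√(2/12) = 0.41σ. P(|difference| > 0.5σ) = 2[1 − Φ(0.5/0.408)] = 2[1 − Φ(1.22)] ≈ 0.22.

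**What the change score carries.** Given a baseline difference D, the change-score difference is shifted by −(1 − ρ)D. With D = 0.5σ and ρ = 0.3 the shift is 0.7 × 0.5 = 0.35σ in size.

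**Variance.** Per patient, the change score has variance 2σ²(1 − ρ). The baseline-adjusted residual has σ²(1 − ρ²). The ratio is (1 + ρ)/2. Since 2(1 − ρ) = (1 − ρ²) + (1 − ρ)², the excess is exactly the variance contributed by chance imbalance. Lost precision and conditional bias are therefore one problem, to be counted once.

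**Small-sample correction.** Estimating q covariates inflates the variance by 1 + q/(N − q − 3). For age and sex this is 1 + 2/19 = 1.105; for age, sex and baseline it is 1 + 3/18 = 1.167. Their ratio is 1.056. The t quantile moves from 2.086 (20 df) to 2.093 (19 df).

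| ρ | (1 + ρ)/2 | × 1.056 | CI width, σ: planned → with baseline | Change in width | Shift from 0.5σ imbalance |
|---|---|---|---|---|---|
| 0.3 | 0.65 | 0.69 | 2.12 → 1.76 | −17% | 0.35σ |
| 0.5 | 0.75 | 0.79 | 1.79 → 1.60 | −11% | 0.25σ |
| 0.7 | 0.85 | 0.90 | 1.39 → 1.32 | −5% | 0.15σ |
| 0.9 | 0.95 | 1.00 | 0.80 → 0.80 | about 0 | 0.05σ |

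Example at ρ = 0.3: 2 × 2.086 × √(1.40 × 2/12 × 1.105) = 2.12 and 2 × 2.093 × √(0.91 × 2/12 × 1.167) = 1.76.

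**Check by simulation** (12 per arm, 5,000 trials per setting). Variance ratios were 0.70, 0.81, 0.90 and 1.00. With a 0.5σ imbalance the mean shift of the change-score estimate was −0.35, −0.24, −0.15 and −0.05σ; with baseline in the model it was within 0.01σ of zero.

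**Sensitivity.** With 10 per arm, close to the 80% completion goal (24 × 0.8 = 19.2), the CI-width ratios are 0.84, 0.90, 0.96 and 1.01. If the entry thresholds compress the baseline spread, the gain shrinks. For example, with slope 0.5, residual variance 0.75 and baseline variance halved to 0.5, the large-sample ratio is 0.75/(0.75 + 0.5² × 0.5) = 0.86 instead of 0.75.

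**The case against.** The strongest reply is that this is an efficiency matter in the secondary outcomes of a feasibility pilot. Change-score analysis is valid under randomisation, and the bias is conditional on the imbalance that happens to occur. That stands, and it limits the weight of the point. So does the fact that the gain vanishes at ρ near 0.9.

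It can also be said that the article does not call age and sex the only covariates, and that a condensed article may leave a baseline term unmentioned. This cannot be excluded. But the article does specify the model and its covariates, and nothing in it points to a baseline term. If one is intended, a sentence settles it.

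Three stronger readings are tempting and are not supported:

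- A reader might infer that the ANCOVA estimate is what sizes the full trial. The article bases planning on a separate Hedges-corrected effect size from raw changes. Changing the ANCOVA alone leaves that figure as it is, although it ignores baseline in the same way.
- A reader might infer that the entry thresholds (VAS at least 3, NDI at least 5) bias the comparison through regression to the mean. They apply to both arms, so the effect cancels in expectation and enters only through the chance imbalance already counted.
- A reader might take the large-sample ratio (1 + ρ)/2 as the gain, which gives CIs 8 to 19% narrower for ρ from 0.7 down to 0.3. That overstates what adding a third covariate achieves with 24 patients.

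Nor do the documents show that age and sex should be dropped. They give nothing on how prognostic either is, so demoting them would be a preference.

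**Conclusion.** The point holds as a modest, specific improvement to the reported secondary analysis. The planned estimate is valid on average, but it leaves uncorrected the share (1 − ρ) of any baseline imbalance. An imbalance above 0.5 SD has roughly a one-in-five chance for each outcome. Except at very high ρ, its CI is also wider than it need be, by the amounts in the table.

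These sizes rest on 1:1 allocation, equal SDs at the two visits, age and sex unrelated to outcome, and an assumed ρ. The article gives no correlation for VAS, NDI or posture, and ρ may differ between them.

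The link to the full trial is indirect. The raw-change effect sizes used to choose between the patient-reported outcomes and to set the sample size carry the same uncorrected imbalance, but they come from a different calculation from the ANCOVA.

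**What to change.** In Statistical analysis, state that each ANCOVA includes the baseline value of the same outcome as a covariate, with age and sex kept if wished. The treatment estimate is then identical whether the dependent variable is change or the follow-up value.

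Add that the baseline-adjusted difference and its 95% CI will be reported beside the Hedges-corrected effect sizes, and considered with them when the full trial's primary outcome is chosen and its size is set.

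The cost is two sentences and one degree of freedom (20 to 19 with 24 complete cases), with no new data. At ρ near 0.9 the extra covariate makes the CI about 0.5% wider with 12 per arm and about 1.4% wider with 10 per arm, which is negligible against the protection gained at lower ρ.

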**Methods/design:**

This pilot, single-blind, randomized controlled trial will divide 24 patients into two groups (study and control) using block randomization. Both groups will receive conventional treatment consisting of a moist hot pack, soft tissue mobilization, manual therapy and therapeutic exercise. The study group will undergo ambulatory mirror-image functional re-training wearing a 3D adjustable CTPCO. The primary outcome is feasibility, including recruitment (e.g., time to complete enrolment, recruitment rate), patient retention and adherence to treatment allocation (e.g., session attendance, home practice, use of non-study treatments). The secondary outcomes used to assess the effectiveness of the treatment will include neck pain (measures using the visual analogue scale (VAS)) and neck disability (measures using the neck disability index (NDI)), among other outcome measures, compared between the experimental and control groups. Three-dimensional posture parameters of head measurements will be provided by a Global Posture System (GPS). The outcome measures for determining the treatment effect will be assessed at three intervals: pre-treatment, after 10 weeks of intervention and after 3 months at follow-up.

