With these considerations in mind and to integrate the findings of 3D postural assessment into the treatment programme, we designed an adjustable cervico thoracic posture corrective orthotic (CTPCO) to be worn by the patient for a short time. The device has the ability to reflect all transitional displacements and rotational movements of the head. Ambulatory exercises will be performed using a treadmill while the CTPCO holds the patient’s reverse posture.

We designed a randomized two-arm pilot trial to investigate the hypothesis that the addition of a 3D adjustable CTPCO to a multimodal programme will produce short- and long-term improvement effects on NSNP management outcomes (i.e., neck pain, neck disability and 3D posture parameters of the head).

The primary aim of this study is to evaluate the feasibility of conducting a larger randomized trial that considers recruitment, compliance to study protocols and adverse events. The secondary aim is to investigate the effect size of the addition of ambulatory mirror image functional re-training via the wearing of a 3D adjustable CTPCO compared to control group interventions for neck pain, disability and 3D posture parameters.

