## Methods/design

### Study design

The study will be a single-blind superiority pilot randomized control trial (RCT) with two parallel groups. The study will be performed according to SPIRIT [25] and good clinical practice guidelines (SPIRIT checklist, Additional file 1). The Ethical Committee of Tongji Hospital, Tongji Medical College, Huazhong University of Science and Technology (HUST), Wuhan, China approved the study protocol (certificate of approval number TJ-IRB20170703), which is prospectively registered at ClinicalTrials.gov (NCT03331120). The study will be performed in the Rehabilitation Department at Tongji Hospital, Affiliated with HUST, China.

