**Fig. 6 Fig6:**
[figure not shown]
Three-dimensional posture parameters measured by the GPS device. The postural parameters of the head in relation to the thoracic region: Postural translation A1 (Tz), A2 (Tx) measured in centimetres. Postural rotations B1 (RZ), B2 (Ry), B3 (Rx) measured in degrees

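### A feasibility and effect-size pilot states an efficacy hypothesis and applies an unadjusted P < 0.05 rule to up to 14 secondary comparisons, which conflicts with its own aims

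*Protocol article*

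**What the plan says.** The last paragraphs of the Background give two aims: feasibility of a larger trial (primary) and the size of the effect of adding the orthosis (secondary). Just before them stands a hypothesis that the addition "will produce short- and long-term improvement effects on NSNP management outcomes (i.e., neck pain, neck disability and 3D posture parameters of the head". The Abstract's Background has a similar hypothesis. The Study design section describes a "single-blind superiority pilot randomized control trial (RCT) with two parallel groups". The Abstract's Methods/design says: "The secondary outcomes used to assess the effectiveness of the treatment will include neck pain", and goes on to disability and other measures.

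Under Statistical analysis, feasibility is tabulated and set against preset goals, without tests. For every secondary outcome the two groups are compared on their change since baseline, and these differences "will be determined and reported as the means and 95% CI, using an analysis of covariance", adjusted for age and sex. The closing sentence applies to all analyses "with significance set at *P* < 0.05". Because feasibility is only described, that threshold bears on the secondary outcomes alone.

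The secondary outcomes are VAS, NDI and five head-posture parameters: "Postural translation A1 (Tz), A2 (Tx) measured in centimetres. Postural rotations B1 (RZ), B2 (Ry), B3 (Rx) measured in degrees". Vertical translation (Ty) is excluded under Measured items. The Data collection section and Table 1 place VAS, NDI and posture at baseline, 10 weeks and the 3-month follow-up.

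**The concern.** The article describes two kinds of study. One estimates feasibility and effect sizes, and needs no significance threshold for efficacy. The other tests a superiority hypothesis on pain, disability and posture, and does have one. The second description is attached to many comparisons in a small sample for which the article gives no effect size, standard deviation or power.

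A report that follows the text could therefore present one significant posture parameter at one visit as support for the hypothesis. The chance of at least one such result with an ineffective device is several times the nominal 5%. At stake is how the pilot's efficacy results are read, and through that the case made for a full trial.

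**Working it through.** The article states no family-wise error rate, so there is no figure to reproduce. The check counts the comparisons and works out the error rate under one possible reading of the results.

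**Inputs from the article.** Per-test level 0.05 (Statistical analysis). Outcomes: VAS, NDI, Tx, Tz, Rx, Ry and Rz, so 2 + 5 = 7. Post-baseline visits: 2. Patients: 24.

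**Assumptions.** Two-sided tests, because the level is paired with 95% intervals; 12 patients per arm; no true effect on any outcome. Correlations between outcomes and between visits are not given, so they are varied.

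**Number of tests.** 7 × 2 = 14. If the change to follow-up in Statistical analysis means a single visit, there are 7. The Interventions section uses the follow-up term for both the 10-week and the later assessment, so 14 is the more natural count, though not a certain one.

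**Independent tests, at least one P < 0.05.**
- 14 tests: 1 − 0.95^14 = 0.512
- 7 tests: 1 − 0.95^7 = 0.302
- Expected number of false positives with 14 tests: 14 × 0.05 = 0.7
- False benefit only, 14 tests: 1 − 0.975^14 = 0.298

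**Correlated tests.** Null trials were simulated with a linear model containing group and two covariates, which leaves 24 − 4 = 20 residual degrees of freedom. With one common correlation across all tests, the chance of at least one significant result in either direction is:

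| Correlation | 14 tests | 7 tests |
|---|---|---|
| 0 | 0.511 | 0.300 |
| 0.3 | 0.444 | 0.277 |
| 0.5 | 0.356 | 0.236 |
| 0.8 | 0.204 | 0.154 |

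A second simulation of 14 tests let the correlation between outcomes differ from that between visits:

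| Between outcomes | Between visits | Either direction | False benefit only |
|---|---|---|---|
| 0 | 0.5 | 0.485 | 0.278 |
| 0.3 | 0.7 | 0.427 | 0.224 |
| 0.5 | 0.8 | 0.348 | 0.176 |
| 0.7 | 0.9 | 0.251 | 0.125 |

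For 14 tests, the two tables together give about 20% to 51% in either direction. A false benefit alone runs from about 13% (last row) to 30% (independence). The 13% belongs to the 0.7/0.9 case; a false benefit was not separated out at the common correlation of 0.8 that produces the 20%.

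**The all-outcomes reading.** If support required every comparison to succeed, the false-positive chance could not exceed that of a single test, 0.05.

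**The case against.** The strongest reply is that no decision in the article rests on a P value. The Primary outcome measure section picks the full trial's primary outcome by the largest between-group effect size, provided the difference exceeds the minimal important change. The Sample-size calculation section passes effect sizes to the next trial. Statistical analysis already plans Hedges-corrected effect sizes and mean differences with 95% intervals. The Abstract's Discussion and the Limitations section present the results as informing the design and feasibility of a larger trial. All of this stands, and it limits the weight of the point.

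Three stronger readings are tempting and are not supported:

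- A reader might infer that the plan counts any one of 14 significant results as success. No section says so, and the Background hypothesis can be read as requiring improvement on all its outcomes, short and long term.
- A reader might take one in three as the plan's error rate. That figure needs a correlation near 0.5 between outcomes, which the article does not give, and it combines benefit with harm.
- A reader might add that non-significant results would be taken as proof of no effect. That is a matter of power, not of multiple testing, and the article does not say null results will be read that way.

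It is also fair to say that a test hierarchy, an alpha split or an exploratory label is often left to a statistical analysis plan, which is not shown here. Their absence alone would be no finding. What the reply does not remove is the text the article does fix: an efficacy hypothesis, a superiority label, an effectiveness role for the secondary outcomes, and a significance threshold over all of them, beside aims that call for none of these.

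**Conclusion.** The point holds as an inconsistency between the stated aims and the stated inference. The text permits significance claims on up to 14 secondary comparisons, which do not fit a pilot aimed at feasibility and effect size.

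The error rates are conditional on any single significant result being read as support. On that condition, and with no true effect, they are about 20% to 51% in either direction for 14 tests, about 15% to 30% for 7, and about 13% to 30% for a false benefit with 14. They also rest on two-sided tests, equal arms and assumed correlations.

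Feasibility is primary, the affected outcomes are secondary, and the planning decisions use effect sizes. The weight is minor to moderate, and nothing here shows that the trial was meant to be confirmatory.

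**What to change.** In Statistical analysis, remove the P < 0.05 rule for the secondary outcomes. State that the between-group differences and effect sizes for VAS, NDI and the posture parameters are exploratory, are reported with unadjusted 95% confidence intervals, and support no claim of effectiveness. Then bring four other places into line with the estimation aim: the hypothesis in the Abstract's Background, the effectiveness wording in the Abstract's Methods/design, the hypothesis in the Background, and the superiority label under Study design.

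The estimates and intervals are already planned, so no data, patients or analyses are added. The downside is that the pilot can no longer report a significant efficacy result. No multiplicity adjustment is needed once the threshold is gone.
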